## Background

Mechanical ventilation (MV) support is crucial for patients with acute respiratory distress syndrome (ARDS). While there is agreement on the preference for lower tidal volumes [1, 2], there is relatively little consensus on the selection of positive end-expiratory pressure (PEEP) [3–9]. Traditionally, lower PEEP has been used [10, 11], but low PEEP can lead to increases in oxygen desaturation and hypoxaemia [4, 12] and worsening of lung injury, indicated by greater use of rescue therapies and deaths after rescue therapy [9]. High PEEP can increase alveolar recruitment, but can decrease cardiac output and lead to further lung injury due to barotrauma and/or volutrauma [13] or overdistension [4, 9].

PEEP can be optimised to reduce hypoxaemia [6] and intrapulmonary shunting [7] and improve gas exchange [8] and oxygenation [4, 14, 15], by maintaining recruitment of injured or collapsed alveoli [13]. In patients with ARDS, PEEP reduces ventilator-induced lung injury (VILI) [4, 9], increases recruitment [14–16], and reduces inflammatory mediators in plasma and bronchoalveolar lavage fluid [8]. MV strategies combining low tidal volumes with recruitment manoeuvres (RMs) and higher PEEP to prevent VILI have been hypothesized as ideal for lung protection [6, 17]. However, currently, there is still no standardized approach to the selection of this optimal PEEP, or to deciding how often PEEP should be adjusted or recalculated.

Reports from experimental animal trials performed by Carvalho et al., Suarez-Sipmann et al. and Lambermont et al. [18–20] indicate that pigs induced with ARDS experience minimal respiratory elastance at a specific PEEP associated with higher oxygenation, maximum recruitment, and higher functional residual capacity, all without signs of lung overdistension. Equally, it has been proposed that PEEP should be set whereby the lung has minimal respiratory elastance (or maximum compliance), which could be clinically beneficial by balancing the risks of PEEP that is set too low or too high [21–23]. Aside from the work by Suter et al. [21], Pintado et al. also showed that PEEP selection at minimal elastance is beneficial to patients [22]. Despite some consistent findings, the application of minimal elastance PEEP selection remains limited and hindered by the lack of an objective, reliable, and easy-to-use method to determine elastance at the bedside in real time.

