## Methods and trial design

### Study design and setting

The CURE RCT is a two-arm RCT comparing model-based mechanical ventilation (MBV) with current standard practice mechanical ventilation (SPV) in patients with a ratio of partial pressure of arterial blood oxygen (PaO2)/fraction of inspired oxygen (FiO2) (P/F ratio) ≤ 200. It is to be conducted in a single-centre hospital intensive care unit (ICU) at Christchurch Hospital in Christchurch, New Zealand.

The primary objective is to assess the impact of model-based ventilation in PEEP selection (MBV) therapy on clinically significant patient outcomes and patient-centred quality of care metrics. The other objectives of this study include (1) to provide the knowledge and methods to make care more patient-specific and timely to optimise treatment and improve outcomes in a large cohort of critically ill patients and (2) to improve the understanding of the pathophysiological basis of critical illness through what we learn about the hourly and daily evolution of lung injury in terms of patient-specific elastance and response to care through this study.

The primary outcome of this study is the area under the curve (AUC) of PaO2/FiO2 over the period of mechanical ventilation. Secondary outcomes include length of time of MV (LoMV), ventilator-free days (VFD) up to 28 days, ICU and hospital length of stay (LoS), AUC of SpO_2_ (oxygen saturation)/FiO_2_ during MV, number of desaturation events (frequency and fraction of time SpO_2_ < 88%), changes in respiratory mechanics and chest x-ray index scores, rescue therapies (prone positioning, nitric oxide use, extracorporeal membrane oxygenation (ECMO)) and hospital and 90-day mortality. These outcomes and their corresponding four levels of specification based on Zarin et al., 2011 is shown in Table 1. The secondary analysis includes comparison of the means of LoMV, VFD, hospital and ICU LoS, 90-day mortality, chest x-ray index scores and rescue therapies used.

**Table 1 Tab1:** Four levels of specification in primary and secondary outcomes

Level 1 Domain	Oxygenation		MV		Length of stay			Other	
Level 2 Specific domain	AUC P/F ratio	AUC Spo2/FiO2	Length of MV	Ventilator free days (VFD) up to 28 days	Hospital	ICU	90-Day mortality	Chest x-ray index scores	Rescue therapies
Level 3 Specific metric	Difference in AUC		Number of days	28 days – days of MV	Number of days		Time to event	Index scores over period of MV	Number of therapies used

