#### P/F ratio criteria

The P/F ratio criteria are:
If the P/F ratio is ≤ 200, the patient is eligible for enrolmentIf 200 < P/F ratio ≤ 300, set FiO_2_ = 50% and PEEP = 5 cmH_2_O and repeat the analysis of arterial blood gases (ABG) within 10 min of the change to measure the new P/F ratio
If the new P/F ratio is ≤ 200, the patient is eligible for enrolmentIf the new P/F ratio is > 200, the patient is not eligible for enrolment and, if appropriate, will be re-screened at a later time

This trial will recruit patients who have a P/F ratio ≤ 200, a criterion in the definition of severe to moderate ARDS as defined by the ARDS Definition Task Force in the Berlin definition [26]. They will be eligible if their P/F ratio is ≤ 200 on any level of PEEP and FiO_2_. Those patients with a 200 < P/F ratio ≤ 300 will be placed on PEEP = 5 cmH_2_O, and FiO_2_ = 50%. If a subsequent P/F ratio is ≤ 200 they will also become eligible (see Additional file 1). The P/F ratio measured at FiO2 of 50% and PEEP of 5cmH_2_O is based on Villar et al. 2013 [27].

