### ABG recordings

The primary outcome of this trial is the AUC of the P/F ratio. For this reason, mandatory daily ABG recordings are performed for up to 10 days after enrolment. ABGs are taken around 0600 hours and 1800 hours. The ABGs are also acquired within 60 min of any recruitment manoeuvre procedure and 30–60 min after the recruitment manoeuvre procedure. The added ABGs from RM procedures will be used in secondary analysis, but will be omitted during primary analysis to ensure the same number of data points per day for all patients.

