### Study outcome

The trial will utilise a primary composite end point incorporating the AUC of the P/F ratio over the period of MV. Every participant in the intervention (MBV) group is compared with every participant in the control (SPV) group. Test statistics will be calculated using the one-sided Wilcoxon rank sum test at alpha of 0.05. If results show no statistically significant difference between the intervention and control, it will result in the rejection of the intervention treatment as a standard of care and thus, the secondary clinical outcome assessments will include the number of desaturation events measured as peripheral capillary oxygen saturation < 90%, LoMV, VFD for 28 days, the quality of mechanical ventilation care measured as the AUC of SpO_2_/FiO_2_ and chest x-ray index scores over time. The test statistic will be calculated using the one-sided Wilcoxon rank sum test at alpha of 0.05.

A difference in the primary outcome will show the impact of MBV compared to SPV. No difference would show that enhanced, model-based metrics of the patient-specific condition have no effect on patient-centred or clinical outcomes. Either outcome will yield clinical guidance.

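### The primary P/F AUC is read at each arm's own PEEP, so it measures oxygenation under each strategy, and a null result cannot show that MBV has no clinical effect

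*Protocol article*

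**What the plan says.** Study design and setting defines the endpoint: "The primary outcome of this study is the area under the curve (AUC) of PaO2/FiO2 over the period of mechanical ventilation". It describes the primary objective as the impact of MBV "on clinically significant patient outcomes and patient-centred quality of care metrics".

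ABG recordings fixes the sampling by clock time: "ABGs are taken around 0600 hours and 1800 hours". Gases drawn around recruitment manoeuvres "will be omitted during primary analysis to ensure the same number of data points per day for all patients". No PEEP or FiO2 setting is attached to the gases that are kept.

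Under Two-arm RCT and General procedures, PEEP follows the software's minimal-elastance recommendation in MBV and standard practice in SPV. Duration of the intervention keeps the arms apart for up to 10 days.

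Background says PEEP can improve oxygenation, and also warns: "High PEEP can increase alveolar recruitment, but can decrease cardiac output and lead to further lung injury".

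Study outcome states "A difference in the primary outcome will show the impact of MBV compared to SPV". It adds that no difference would show an absence of effect on patient-centred or clinical outcomes, and that a non-significant result leads to rejecting MBV as a standard of care.

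**The concern.** The quantity measured depends on the setting that is randomised. A patient's P/F at 0600 reflects the state of the lung and the pressure applied at that moment. A difference between arms can come from either, and so can the lack of one.

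That would be harmless if the conclusion stayed with oxygenation. Study outcome goes further and lets a null P/F AUC stand for a null clinical effect, with rejection of MBV attached. If MBV settled at lower PEEP than SPV, a real improvement in the lung could be offset at sampling and the intervention rejected. If MBV settled at higher PEEP, oxygenation could look better with an unchanged or injured lung. A reader applying the section as written would draw the wrong conclusion in the first case and could be misled in the second.

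**Working it through.** **1. Is the primary P/F tied to a setting?**

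| Where | When P/F is read | PEEP and FiO2 |
|---|---|---|
| P/F ratio criteria, entry at or below 200 | at screening | any |
| P/F ratio criteria, 200 to 300 | repeat gas within 10 min | PEEP 5 cmH2O, FiO2 50% |
| ABG recordings, primary outcome | about 0600 and 1800 | PEEP as set in the arm; FiO2 titrated to SpO2 targets |

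For the middle row the protocol says "Those patients with a 200 < P/F ratio ≤ 300 will be placed on PEEP = 5 cmH_2_O, and FiO_2_ = 50"%, and the repeat value decides eligibility. A repeat gas so soon after a change of settings is useful only if settings can move P/F across 200. The protocol does not state that reason; it is an inference, though it agrees with the Background text that PEEP affects oxygenation.

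**2. What can the endpoint tell apart?**

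| PEEP in MBV relative to SPV | Lung in MBV | Possible P/F AUC result |
|---|---|---|
| higher | unchanged or worse | favours MBV |
| higher | better | favours MBV |
| lower | better | no difference |
| lower | unchanged | no difference, or favours SPV |

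The first two rows look alike, and the last two can. P/F AUC alone does not separate them.

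**3. How large would a setting effect have to be?**

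The protocol gives no figure for this. Its 160 per arm (Sample size study) rests on a 25% reduction in median LoMV with an unstated distribution, so it cannot be reproduced here. It is taken as given.

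Inputs from the protocol: n = 160 per arm and a one-sided Wilcoxon test at 0.05. Assumed: a normal shift in a patient's average P/F, Wilcoxon efficiency 0.955, and the SDs and shifts below.

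- Effective n = 160 × 0.955 = 152.8. Standard error in SD units = √(2/152.8) = 0.1144.
- Just-significant observed difference = 1.645 × 0.1144 = 0.19 SD.
- True shift detected with 80% probability = (1.645 + 0.842) × 0.1144 = 0.28 SD.
- Probability of significance = Φ(shift/(SD × 0.1144) − 1.645). For a shift of 10 mmHg and SD 65: Φ(1.345 − 1.645) = Φ(−0.300) = 0.38.

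Probability that a shift from PEEP alone, in MBV's favour, is significant:

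| Shift (mmHg) | SD 50 | SD 65 | SD 80 |
|---|---|---|---|
| 5 | 0.22 | 0.17 | 0.14 |
| 10 | 0.54 | 0.38 | 0.29 |
| 15 | 0.84 | 0.65 | 0.50 |
| 20 | 0.97 | 0.85 | 0.71 |
| 30 | 1.00 | 0.99 | 0.95 |

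In the opposite direction, suppose a lung gain of 0.2845 SD (80% power alone) meets an opposing setting effect of 0.1882 SD, and the two add. The net is 0.0963 SD, 0.0963/0.1144 = 0.842, and the power is Φ(0.842 − 1.645) = Φ(−0.803) = 0.21.

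**4. Would the oxygenation index settle it?**

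The index is 100 × FiO2 × mean airway pressure / PaO2, which is 100 × mean airway pressure / (P/F). At equal P/F it rises in proportion to pressure, so it counts against the higher-pressure arm by construction. It shows whether a P/F difference survives accounting for pressure. It does not isolate lung condition.

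**The case against.** The strongest reply is that MBV is a strategy for choosing PEEP. Under intention to treat, oxygenation at the PEEP it chooses is its effect, and an effect carried by the randomised element is not confounding. This stands: the sentence "A difference in the primary outcome will show the impact of MBV compared to SPV" is true in that sense, and the protocol never says that a higher AUC proves a better lung. The patient-centred wording is attached only to the no-difference sentence. The parallel text after Table 1 refers to primary and secondary outcomes together.

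Other points also stand. Table 1 files AUC P/F under oxygenation. Respiratory mechanics and chest x-ray scores are already secondary outcomes. Patients at or below 200 enter on any settings, so fixed settings are not the protocol's general standard for P/F. Reading a non-significant result as proof of no effect would be a fault with any endpoint.

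Common SpO2 targets align how FiO2 is chosen, and omitting gases around manoeuvres equalises the number of samples. Neither removes the influence of PEEP at 0600 and 1800. LoMV, VFD and mortality are collected, but the rejection rule is tied to P/F AUC.

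A reader might infer that MBV will run higher PEEP and that the endpoint is therefore biased towards it. The protocol does not support this. It does not say which arm will be higher, and SPV after a staircase manoeuvre may be set between 16 and 24 cmH2O.

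**Conclusion.** The point holds as a limit on interpretation. AUC P/F is a legitimate measure of oxygenation under each PEEP strategy. It cannot by itself distinguish a better lung from applied pressure, in either direction, and a null result on it does not show that MBV lacks effect on patient-centred or clinical outcomes. Using that null to reject MBV as a standard of care goes beyond what the endpoint can carry, given the clinical objective in Study design and setting.

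The facts about sampling and randomised PEEP come from the protocol. The size does not: the SDs, shifts and additivity above are assumptions, and they show only that a modest setting effect could matter at this sample size. The documents do not support the stronger readings that the primary endpoint is invalid, that the comparison is confounded, or that the bias has a known direction.

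**What to change.** In Study outcome, state that a difference or no difference in AUC P/F concerns oxygenation on the assigned ventilator settings only. Delete the inference from no difference to no effect on patient-centred or clinical outcomes, and do not rest rejection of MBV on it. Rest clinical claims on LoMV, VFD and mortality. Check the parallel sentences after Table 1 for consistency.

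Report PEEP and mean airway pressure at the 0600 and 1800 gases by arm and day. Add one analysis that accounts for pressure, such as the AUC of the oxygenation index on the same gases. Label it supportive and do not make it a co-requirement, because it penalises the higher-pressure arm by construction.

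The cost is a few sentences, a tabulation and one derived variable. Airway pressure is already recorded in both arms, and no clinical setting or sampling time changes. The downside is that a positive or a null P/F result must be worded more narrowly.

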### Sample size study

A Monte-Carlo simulation was performed to determine the sample size and determined that a minimum effective sample size of approximately 160 patients per arm is required to identify a 25% reduction in median LoMV, with 0.8 power, at a double-sided significance level of 5% [37].

### Stopping rule

A linear alpha spending approach will be used for early termination of the trial for safety. Linear alpha spending falls between a Pocok and O’Brien-Fleming boundary [38]. With analysis points of 50, 75, 100, 125 and 160 patients per arm, and assumed control group mortality of 0.2, the mortality difference required to stop the trial (Mortality_Intervention_ – Mortality_control_) at each analysis point respectively is 0.20, 0.16, 0.14, 0.12 and 0.10. This approach has cumulative α = 0.025.

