**Methods and design:**

The CURE RCT compares two groups of patients requiring invasive MV with a partial pressure of arterial oxygen/fraction of inspired oxygen (PaO2/FiO2) ratio ≤ 200; one criterion of the Berlin consensus definition of moderate (≤ 200) or severe (≤ 100) ARDS. All patients are ventilated using pressure controlled (bi-level) ventilation with tidal volume = 6–8 ml/kg. Patients randomised to the control group will have PEEP selected per standard practice (SPV). Patients randomised to the intervention will have PEEP selected based on a minimal elastance using a model-based computerised method. The CURE RCT is a single-centre trial in the intensive care unit (ICU) of Christchurch hospital, New Zealand, with a target sample size of 320 patients over a maximum of 3 years. The primary outcome is the area under the curve (AUC) ratio of arterial blood oxygenation to the fraction of inspired oxygen over time. Secondary outcomes include length of time of MV, ventilator-free days (VFD) up to 28 days, ICU and hospital length of stay, AUC of oxygen saturation (SpO_2_)/FiO_2_ during MV, number of desaturation events (SpO_2_ < 88%), changes in respiratory mechanics and chest x-ray index scores, rescue therapies (prone positioning, nitric oxide use, extracorporeal membrane oxygenation) and hospital and 90-day mortality.

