### Randomisation and blinding

Participants will be block-randomised, with block sizes generated using a randomisation programme. The programme will randomly assign patients into either a control group or intervention group through a random block size (the block size is 4, 6, 8 or 10 patients). Eligible and consented patients will be block-randomised in a ratio of 1:1. No effort will be made to stratify the subgroups considered in the secondary analyses. By the nature of the intervention, CURE cannot be double-blinded. Un-blinding is not applicable due to the nature and setting of the intervention.

All patient data collected are de-identified using a single patient numbering system. Patients are assigned to a study number to ensure no bias in the results. This system will be a simple incrementing scheme, such that patients randomised into the CURE trial are identified as study-001, study-002, etc.

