### CURE RCT composition

The steering committee of the CURE RCT comprises the primary investigators [name], [name], [name] and [name]. The clinical data are collected by research nurses in the ICU and mechanical ventilation data and oxygenation (bedside monitor) data will be collected by researchers from the UC. All study data will be stored in the double-encrypted repository at UC. Data will be interpreted by participating researchers. The open and closed case interim reports will be compiled by [name] every 6 months and when 50 and 100 patients have been included. The DMC will have authority to continue or stop of the trial based on the interim reports.

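### The mortality stopping boundaries are fixed absolute differences that give α of 0.025 only near 20% control mortality, and the DMC report schedule does not match the five planned looks

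*Protocol article*

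**What the plan says.** The Stopping rule section of the protocol article states: "A linear alpha spending approach will be used for early termination of the trial for safety". It then sets the looks and the planning rate: "With analysis points of 50, 75, 100, 125 and 160 patients per arm, and assumed control group mortality of 0.2". The mortality difference, intervention minus control, needed to stop "at each analysis point respectively is 0.20, 0.16, 0.14, 0.12 and 0.10", and "This approach has cumulative α = 0.025". Nothing is said about what happens to these differences if control mortality is not 20%.

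The CURE RCT composition section schedules the open and closed interim reports "every 6 months and when 50 and 100 patients have been included" and adds: "The DMC will have authority to continue or stop of the trial based on the interim reports". It does not give the unit of the 50 and 100, and it does not refer to the boundaries.

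**The concern.** The variance of a difference between two proportions depends on the event rate. A threshold fixed in absolute terms therefore corresponds to a different significance level at each mortality rate, and the quoted α belongs to the rule together with the 20% assumption. If mortality is higher, the trial could be stopped for harm by chance more often than stated. If it is lower, real harm is less likely to trigger the rule.

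The second issue is whether the DMC will have a report when a boundary applies. The looks are counted per arm. The reports are counted in patients, with the same 50 and 100 recurring without a unit, and the DMC decides on those reports.

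**Working it through.** **Inputs.** From Stopping rule: looks at n = 50, 75, 100, 125 and 160 per arm; differences d = 0.20, 0.16, 0.14, 0.12 and 0.10; control mortality p = 0.20; cumulative α = 0.025, one-sided because only excess deaths on the intervention count; linear spending. From Randomisation and blinding: 1:1 allocation. From the abstract: 320 patients in total, so 160 per arm. Mortality rates other than 20% are an assumed range, because the protocol gives no other figure.

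**Step 1: reproduce the stated α.** With no true difference, z = d / √(2p(1−p)/n), and looks i < j have correlation √(n_i/n_j). At p = 0.20 the first look gives 0.20 / √(2 × 0.2 × 0.8 / 50) = 0.20 / 0.08 = 2.50. The five values are 2.50, 2.45, 2.47, 2.37 and 2.24. The multivariate normal gives cumulative crossing probabilities of 0.0062, 0.0109, 0.0141, 0.0182 and 0.0245. An exact binomial recursion gives 0.0194 if the boundary must be exceeded and 0.0301 if reaching it is enough. These bracket 0.025, so the stated figure is reproduced.

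Solving the linear spending function directly (cumulative α of 0.025 × n/160 at each look) gives z = 2.418, 2.476, 2.426, 2.371 and 2.268. At 20% mortality these are differences of 0.193, 0.162, 0.137, 0.120 and 0.101, matching the protocol to two decimals except at the first look (0.19 against 0.20).

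**Step 2: keep the differences and change the mortality.** At p = 0.30 the first-look z falls to 0.20 / √(2 × 0.3 × 0.7 / 50) = 2.18. Cumulative one-sided α over all five looks:

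| Mortality in both arms | Normal theory | Exact, boundary exceeded | Exact, boundary reached |
|---|---|---|---|
| 10% | 0.003 | 0.002 | 0.004 |
| 15% | 0.012 | 0.009 | 0.015 |
| 20% | 0.0245 | 0.019 | 0.030 |
| 25% | 0.038 | 0.031 | 0.045 |
| 30% | 0.050 | 0.041 | 0.058 |
| 40% | 0.066 | 0.056 | 0.076 |

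Without the 160-per-arm look, which coincides with the end of enrolment, exact α is 0.031–0.047 at 30% and 0.044–0.062 at 40%. The linear function would have spent 0.025 × 125/160 = 0.0195 by then.

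**Step 3: sensitivity when mortality is low.** With 10% control and 20% intervention mortality, the fixed differences stop the trial by the last look with exact probability 0.50 (exceeded) to 0.57 (reached). The linear-spending z boundaries, applied to the observed pooled mortality, stop it with probability 0.65 (1,000,000 simulated trials).

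**Step 4: test the repair.** With no true difference, simulated α for the pooled z boundaries was 0.0247, 0.0249, 0.0243, 0.0250, 0.0254, 0.0255 and 0.0257 at 10, 15, 20, 25, 30, 35 and 40% mortality. The same z values correspond to differences of 0.222, 0.185, 0.157, 0.137 and 0.116 at 30%.

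**Step 5: set looks against reports.** The planned looks are at 100, 150, 200, 250 and 320 patients in total.

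- If 50 and 100 are totals, the reports fall at 25 and 50 per arm. The first has no boundary and the second meets look 1, so one of five looks is covered.
- If they are per arm, they meet looks 1 and 3, so two of five are covered.
- On neither reading does a count trigger a report at 75, 125 or 160 per arm.
- Assuming even accrual of 320 patients, six-monthly reports fall at 32, 64, 96, 128 and 160 per arm over 30 months, or about 27, 53, 80, 107, 133 and 160 over 36 months. Apart from the final total, none is exactly a planned look.

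**The case against.** The rule is not wrong on its own terms. The protocol states the 20% assumption openly and α follows from it. Quoting boundaries as risk differences at a planning rate is common, and a DMC charter that is not shown could provide for rescaling. That stands, so the point is an improvement to a rule that is correct at its planning rate.

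A reader might infer from the adverse event section, which expects high baseline mortality, that 20% is too low and that α is inflated in practice. The documents do not support this. That remark carries no figure, 20% is compatible with it, and the exclusion criteria remove moribund patients and those not expected to survive 72 hours or 90 days. The true rate could lie on either side.

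A reader might also take the 50-patient report as 25 per arm and suppose that the 0.20 boundary would be applied there. At 20% mortality that single look has an exact false-stop probability of 0.025 (exceeded) to 0.055 (reached), against 0.004 to 0.009 at 50 per arm. But the section does not say the count is a total, and nothing tells the DMC to use the boundary there. Routine reports can exist alongside formal looks. What remains is an undefined unit and looks without a triggered report.

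Finally, the rule concerns harm only. Inflated α means more false stops for harm and no inflation of the efficacy error. The DMC retains judgement.

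**Conclusion.** The point holds as a moderate weakness in the safety monitoring. The stated α of 0.025 is correct at 20% control mortality, but the rule does not keep it at other rates. Over the assumed range of 10% to 40%, exact α runs from 0.002–0.004 to 0.056–0.076 and is already 0.031–0.045 at 25%. The error has a direction: above 20% false stops for harm become too frequent, while below 20% the 0.025 limit is respected and the cost is reduced sensitivity (0.50–0.57 against 0.65 for a rise from 10% to 20%). The documents do not show which side of 20% the trial will fall.

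The schedule conflict rests on no assumed rate: count-triggered reports serve one or two of the five looks, depending on the unit. The primary analysis and sample size are unaffected, and the 160-per-arm look cannot stop enrolment early.

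**What to change.** In Stopping rule, state the boundaries as linear-spending critical values for the pooled z statistic at the observed overall mortality: about 2.42, 2.48, 2.43, 2.37 and 2.27 at 50, 75, 100, 125 and 160 per arm. Recompute them from the spending function if a look moves. Say whether stopping requires reaching or exceeding the boundary, and keep the absolute differences only as illustrations at 20% mortality.

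In CURE RCT composition, give the unit of the patient counts, trigger a report at each planned look (100, 150, 200, 250 and 320 in total), and state that the six-monthly and any other reports carry no formal boundary and spend no α.

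The cost is wording in the protocol and any DMC charter. The change keeps the chosen spending function, the five looks and the 0.025, and needs no extra data. The Trial status section says recruitment has not started, so it can be made before any look.
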